# A cluster randomized controlled trial of extending ART refill intervals to six-monthly for anti-retroviral adherence clubs

**DOI:** 10.1186/s12879-019-4287-6

**Published:** 2019-07-30

**Keywords:** Extended dispensing intervals, Antiretrovirals, Differentiated service delivery, HIV

## Abstract

**Background:**

The antiretroviral therapy (ART) adherence club (AC) differentiated service delivery model, where clinically stable ART patients receive their ART refills and psychosocial support in groups has supported clinically stable patients’ retention and viral suppression. Patients and health systems could benefit further by reducing visit frequency and increasing ART refills. We designed a cluster-randomized control trial comparing standard of care (SoC) ACs and six-month ART refill (Intervention) ACs in a large primary care facility in Khayelitsha, South Africa.

**Methods:**

Existing ACs were randomized to either the control (SOC ACs) or intervention (Intervention ACs) arm. SoC ACs meet five times annually, receiving two-month ART refills with a four-month ART refill over year-end. Blood is drawn at the AC visit ahead of the clinical assessment visit. Intervention ACs meet twice annually receiving six-month ART refills, with a third individual visit for routine blood collection anytime two-four weeks before the annual clinical assessment AC visit. Primary outcomes will be retention in care, annual viral load assessment completion and viral load suppression. (<400copies/mL) after 2 years.

Ethics approval has been granted by the University of Cape Town (HREC 652/2016) and the Medecins Sans Frontieres (MSF) Ethics Review Board (#1639). Results will be published in peer-reviewed journals and made widely available through presentations and briefing documents.

**Discussion:**

Evaluation of an extended ART refill interval in adherence clubs will provide evidence towards novel model adaptions that can be made to further improve convenience for patients and leverage health system efficiencies.

**Trial registration:**

Registered with the Pan African Clinical Trial Registry: PACTR201810631281009. Registered 11 September 2018.

**Electronic supplementary material:**

The online version of this article (10.1186/s12879-019-4287-6) contains supplementary material, which is available to authorized users.

## Background

South Africa is home to the largest number of people living with HIV (PLHIV), an estimated 7.9 million people. In 2017, it was estimated that 55.7% of PLHIV in South Africa were on antiretroviral therapy (ART) [1]. In February 2018, the South African president committed to starting another 2 million PLHIV by 2020 towards ensuring South Africa meets its target of 81% by the end of 2020 [2, 3]. To achieve these targets, the already overburdened health system needs to find ways to attract and retain significantly more patients on ART.

Differentiated models of ART delivery for patients that are otherwise healthy and clinically stable on ART, attempt to make ongoing access to ART refills and clinical management more convenient and easily accessible in order to support continued adherence to treatment on a long-term basis. Such models have been shown to be feasible to implement, acceptable to patients with good retention and viral suppression outcomes. These models can also be leveraged to improve health system efficiency in an era with limited resources to achieve ambitious targets [4–8]. One such differentiated ART delivery model is the ART adherence club (AC), originally a demonstration project by Médecins Sans Frontières (MSF) in Khayelitsha, South Africa. The AC model was created to and has supported long-term adherence and retention of clinically stable ART patients [4, 9–14]. It has been endorsed in a number of sub-Saharan African country policies [15–17], including South Africa, where it has been implemented at scale [18].

Novel adaptations to differentiated ART delivery models such as ACs are needed in order to further increase convenience and access for patients and expand ART access within a context of declining resources [19]. One possible adaptation is to reduce the frequency of visits by increasing the amount of ART dispensed at each refill. This would allow for an increase in the number of ACs managed by the same staff complement, and could further decongest facilities, making space for new patients to start ART and for patients receiving an ART regimen that is failing and those presenting to care with advanced HIV disease to be more intensively clinically managed.

In the World Health Organisation’s (WHO) updated 2016 consolidated guidelines on the use of antiretroviral drugs for treating and preventing HIV infection, WHO recommends that clinically stable patients can receive ART refills every 3–6 months [20]. However, there is a paucity of retention and viral suppression evidence supporting longer intervals (e.g. 4–6 months). Evidence beyond 3-month ART refills is needed before health authorities invest in changing their supply chain management system to support such longer ART refills periods (see concerns raised in pre-study engagment, Additional file 1). This study aims to provide high-quality evidence on the effect of extended ART dispensing intervals on sustained retention in care and viral suppression.

## Methods

### Study aims & objectives

The overall aim of this project is to investigate the impact of extended ART dispensing intervals and less frequent psychosocial support on retention in care and viral suppression among clinically stable ART patients in ACs.Primary objectiveTo compare the retention, viral load assessment completion and viral suppression outcomes of patients receiving their ART refill through standard of care (SOC) ACs and six-month ART refill (Intervention) ACs over 24 months.Secondary objectives

To determine:Medicine supply chain feasibility of Intervention ACs implementation, including medicine losses and wastage associated with the six-month supply of ART.Impact of Intervention ACs model on clinic congestion.

### Study design

This is a cluster-randomized control trial to evaluate whether patients in Intervention ACs have non-inferior retention and viral load assessment and viral suppression outcomes compared to those in SOC ACs.

### Setting

The study will take place in Khayelitsha, a peri-urban area home to approximately 500 000 people. The community is of low socioeconomic status with high levels of HIV (antenatal HIV prevalence of 34% in 2016) and high levels of unemployment [21]. The participants will be recruited from Ubuntu Site B clinic’s existing ACs. A summary of the study site is provided in Table 1.

**Table 1 Tab1:** Summary of study site

Site	Total on ART at site end March 2017	Date ACs started at site	Total adults in ART ACs end March 2017
Ubuntu ART clinic, Khayelitsha	10252	2007	4535

### Study population

Participants will be stable HIV-positive adults on ART who are currently in an AC at the study site. ACs will be recruited at their routine AC visit, which occurs five times per year. Study inclusion criteria exist at both AC and individual level.

#### AC inclusion criteria

> 90% of patients in the AC consent to be enrolled in study prior to randomization

#### AC exclusion criteria

ACs catering to patients who require more regular clinical follow-up than a yearly visit (e.g. family ACs, youth ACs)ACs facilitated by nurses with limited group interaction/ support and/or which function more as ART pick-up point (e.g. evening ACs)

#### Participant inclusion criteria

Age 18 years or olderOn ART for at least 6 monthsMost recent documented viral load < 400 copies/mL (not older than 12 months)Able to provide informed consent for research

#### Participant exclusion criteria

Intention to relocate out of Cape Town permanently during the study period

### Description of intervention and control

A description of SOC ACs and Intervention ACs is provided below and summarized in Table 1.

#### The SOC ACs

Participants in the SoC ACs will continue to be provided with their ART refill, clinical care and support following the current Western Cape provincial AC guidelines. At time of protocol submission, SOC ACs were groups of 25–30 stable patients who had been on ART for 6 months or more, had an undetectable viral load, and were referred by a clinician to the model of care. SOC ACs are facilitated by a lay healthcare worker and meet five times per year (bi-monthly with a four-month gap over the end of the year to support migration patterns) for a group support session, a brief symptom check and distribution of pre-packed ART with referral by the lay provider to a nurse based at the clinic if necessary. At one of these visits the patient’s blood is taken by a nurse for routine blood monitoring, including viral load. At the following AC visit, each AC member has their annual clinical assessment with a nurse.

Patients are allowed to send a treatment “buddy” to collect their ART refill to every alternate AC. A treatment buddy is a friend or family member of an AC member requested by the AC member to collect their ART refill at from the AC on the AC member’s behalf.

#### The intervention ACs

The Intervention ACs meet twice annually receiving six-month ART refills, with the patient being asked to individually attend a third visit for routine blood collection anytime two-four weeks before their annual clinical assessment AC visit. Patients in Intervention ACs are not able to send a treatment “buddy” to collect their ART refill to ensure the health system interacts with patient at least twice a year.

In both SOC and Intervention ACs, a five-day grace period is permitted for late attendance. In other words, AC patients need to come within 1 week of their AC visit to collect their ART refill or they are up-referred to the clinician-led ART care based at the clinic. A patient is also up-referred if they experience viral rebound (a viral load of > 400 copies/mL) or develop another clinical condition that requires more regular clinical support (Table 2).

**Table 2 Tab2:** Comparison of SOC ACs and Intervention ACs

	Standard of Care ACs	Intervention six-month ACs
Frequency of AC visits	2-monthly (5 per year)	6-monthly (2 per year)
ART dispensing interval	2-monthly (5 per year)	6-monthly (2 per year)
Frequency of clinical assessments	12-monthly	12-monthly
Frequency of routine bloods	12-monthly	12-monthly
Timing of routine bloods	As part of AC visit	As an additional individual visit, 2–4 weeks before clinical assessment AC visit
Units of care	Groups of 25–30	Groups of 25–30
Peer-based support	Strong emphasis	Strong emphasis
Patient self-management	Strong emphasis	Strong emphasis
Management of clinical complications	Up-referral to clinician-led ART care based at the clinic	Up-referral to clinician-led ART care based at the clinic
ART packing and dispensing	Pre-packed by central dispensing unit, supplied to clinic pharmacy and dispensed at AC visit	Pre-packed at clinic pharmacy with support from study team staff and dispensed at AC visit
Treatment “buddies”*	Allowed to collect at every alternate AC visit	Not permitted
Standard number of contacts per year	5 (all within the AC)	3 (2 within the AC and 1 individual for routine bloods)
Minimum number of contacts per year	3 (could send a “treatment buddy” to collect ART twice)	3 (within the AC and 1 for routine bloods)

### Recruitment - study participation and withdrawal processes

ACs eligible for the study will be offered study participation at a routine AC visit. After the study is explained, the group will be afforded an opportunity to discuss and ask questions. Thereafter each AC member present will be asked to cast their individual vote for study participation on a named voting slip, which will folded and placed in a closed box handled by the study staff. The study staff will exit the venue to count the votes and will return to inform the group of the final outcome (i.e. > 90% voted to participate or ≤ 90% voted to participate) with each individual’s vote remaining confidential and only known to study staff who will not disclose it to any other person.

If more than 90% of the AC members vote in favour of participating in the study, the AC will be enrolled in the study. Consent procedures will take place at the same AC visit, or over the subsequent one or two visits, if patients need more time to consider or were not present at the study enrolment AC visit.

In the case where an individual patient does not vote in favour of study participation, the patient will have the choice to stay in the AC and participate in the study or to transfer to a newly formed AC that is not participating in the study.

AC randomization will take place after all AC patients have provided consent, or arranged to transfer out. Randomization will be performed with the *Randomize* package in Stata, ensuring balance between community and facility ACs in each arm [22]. At the start of the following AC meeting, the study staff will draw an envelope containing the randomization outcome and inform the AC members whether their AC has been allocated to the SOC or intervention arm (see randomization SOP in Additional file 3). The ACs will vote on their continuation in the study for a second time, following the same procedure as the first vote.

At the AC visit after being informed of their AC study arm, groups will be given their first study ART refill.

See Fig. 1 for more details.

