### Sample size and power considerations

As this study is interested in non-inferiority, all statistical tests were one-tailed with an alpha of 0.025 to address type 1 error. At time of protocol development, there were 97 eligible ACs. We assumed 10% of the ACs were would not participate in the study leaving 87 ACs eligible for randomization (approximately 43 per arm), with a total of 1986 participants (993 per arm). We proposed a clustered sampling strategy for our study. There is a paucity of information in the literature regarding correlation between individuals within ACs, therefore we reviewed the literature relating to the clustering effect of facilities. Thus, to account for the correlation within clusters we assumed a correlation ranging from 0.05–0.10 and an average cluster size of 24 [23, 24] resulting in our estimated design effect (deff) ranging from 2.15–3.3. We applied the deff to our total sample size to determine the effective sample size. Assuming retention in care would range from 75 to 85% with a 10% difference in retention in care between the control and intervention groups, we estimated the power of our study to range from 0.80–0.98. See supplementary materials for detailed sample size calculations.

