### Data collection

Following recruitment, ACs that are eligible, consent, and are randomized to the intervention arm will be transitioned to Intervention ACs. Duration of follow-up for patients is identical for patients in both arms of the studies.

Primary outcome data will be extracted from routine clinical records including AC registers, the National Health Laboratory Services, and patient paper and electronic records. Data will be collected for 27 months: 24 from the start of the study, with three additional months of follow-up before closing the dataset to ascertain final outcomes. This will be supplemented by data from the Western Cape provincial health data center, which uses probabilistic matching algorithms to link patient data from different Western Cape facilities, laboratory systems and pharmacy data.

Secondary outcome data related to medicine supply chain feasibility will be collected by the study team in collaboration with the pharmacy staff at the study site onto a lost drug reporting form, and will be compiled in a study database.

Additional data on ART dispensing between study visits and secondary outcome data related to patient visit data will be extracted from the provincial health data system.

Collection of participant names and other identifiers will be restricted to informed consent documents, and a study identification key, all of which will be kept in a locked cabinet in the study office at MSF separate from other study documentation and accessible only by the MSF project coordinator and PI. These records will be destroyed 3 years after completion of the final study report by a company that destroys confidential patient documents. All electronic records will be kept in password-protected files. All electronic communications of study data will be through password-protected, encrypted files.

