### Risks

#### Undue group influence risk

Carrying out an intervention study in a group focused model of care requires a careful balancing of both the group and individual rights to participate or not participate in the study. By recognising that the group itself has a right to benefit from study participation and not to dissolve as result of study participation or non-participation, introduces a risk of undue influence over the individual to consent or refuse study participation. As outlined above in the methods section, the study design and procedures will limit this risk as follows:High thresholds (> 90%) have been set requiring an overwhelming majority of the group to be in favour of study participation for the AC to be included in the study.An additional step with similar thresholds was put in place for AC members to have a further opportunity to consider the AC’s study participation after being informed of the outcome of randomization.When the study is introduced to the group, the study staff will explain that all AC members have the right to refuse participation and doing so will in no way compromise their access to HIV management services.Voting will be confidential.

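### Clubs vote on staying in the trial after learning their arm, and nothing shown keeps a randomised club that votes out in the comparison

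*Protocol article*

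**What the plan says.** The section on recruitment and withdrawal processes gives the order of events: first vote, individual consent, randomisation, announcement of the arm at the next club meeting, second vote, first study refill.

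- The rule for the first vote is: "If more than 90% of the AC members vote in favour of participating in the study, the AC will be enrolled in the study".
- Once the arm has been announced: "The ACs will vote on their continuation in the study for a second time, following the same procedure as the first vote".
- The section on undue group influence confirms the step: "An additional step with similar thresholds was put in place for AC members to have a further opportunity", to be used "after being informed of the outcome of randomization".
- The timeline places the announcement and the clubs' withdrawal process together in Jul/Aug 2017.
- Treatment follows at the next visit: "At the AC visit after being informed of their AC study arm, groups will be given their first study ART refill".

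The power calculation starts from 97 eligible clubs and assumes that 10% do not take part, "leaving 87 ACs eligible for randomization (approximately 43 per arm), with a total of 1986 participants (993 per arm"). It makes no allowance for clubs lost after randomisation. The data analysis section excludes from the clinic-retention denominator anyone who transfers out of the clinic, and from the club-retention denominator anyone who transfers out of the club. It does not mention clubs that vote out.

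**The concern.** Randomisation protects the comparison only if membership of the compared groups does not depend on the allocation. Here a whole cluster decides whether to continue when it already knows its arm. The arms differ in visit frequency, refill length and whether a treatment buddy may collect, so clubs have reasons to vote differently by arm. If clubs that leave differ in retention from clubs that stay, the observed difference shifts. Adjusting for patient covariates cannot be relied on to remove that shift.

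The trial is designed to show non-inferiority. A shift that flatters the intervention arm therefore raises the chance of accepting an inferior model, and a shift the other way makes a true non-inferiority harder to show.

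**Working it through.** **How easily a club leaves.** More than 90% must be in favour. With 24 members, two against gives 22/24 = 91.7% (stays) and three against gives 21/24 = 87.5% (leaves). With 30 members, three against gives 27/30 = 90.0%, which is not more than 90% (leaves). Three opposing votes are enough for any club size from 21 to 30.

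**Reproducing the stated power (0.80-0.98).** Inputs from the sample size section: 993 per arm, average cluster size 24, intracluster correlation (ICC) 0.05-0.10, retention 75-85%, a 10-point difference (read here as the non-inferiority margin), and "all statistical tests were one-tailed with an alpha of 0.025 to address type 1 error".

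- Design effect = 1 + (24 - 1) × ICC = 2.15 and 3.30.
- Effective n per arm = 993/2.15 = 462 and 993/3.30 = 301.
- Power = Φ(0.10/SE - 1.96), with SE = √[2p(1-p)/n] and equal true rates.
- Worst case (ICC 0.10, p = 0.75): SE = 0.0353, power 0.81.
- Best case (ICC 0.05, p = 0.85): SE = 0.0235, power 0.99.

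These agree with the stated range to within about one point.

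**Power after clubs leave (worst case; shares assumed).** For loss of a share f from one arm, SE = √{p(1-p)[1/n + 1/(n(1-f))]}. For loss from both arms, n is replaced by n(1-f).

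| Share of clubs leaving | From one arm | From both arms |
|---|---|---|
| 0% | 0.81 | 0.81 |
| 5% | 0.80 | 0.79 |
| 10% | 0.79 | 0.77 |
| 15% | 0.78 | 0.74 |

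**Bias (all inputs assumed).** If a share f of one arm's clubs leaves and their retention would have been d points lower than in the clubs that stay, that arm's observed retention is too high by f × d.

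- Low end: 0.02 × 5 = 0.1 points.
- Middle: 0.10 × 15 = 1.5 points.
- High end: 0.15 × 15 = 2.25 points. For example, with stayers at 85% and leavers at 70%, the whole arm is at 0.85 × 85 + 0.15 × 70 = 82.75%, but 85% is observed.

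**Effect on the error rate if the intervention arm is the one flattered.** At a true 10-point deficit, the one-sided error is Φ(b/SE - 1.96), where b is the bias and SE uses p and p - 0.10. Across the document's ranges of ICC and retention:

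| Bias b | One-sided error |
|---|---|
| 0 | 0.025 |
| 0.1 points | about 0.027 |
| 1.5 points | 0.06-0.08 |
| 2.25 points | 0.09-0.14 |

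If the SOC arm is the one flattered, the error falls below 0.025 and power is lost instead.

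**The case against.** The strongest reply is that exclusion is not stated. No sentence says that a club voting out is dropped from the analysis. The article is an abridged protocol, and the randomisation procedure file, the study schema and any SAP are not shown. Analysis sets are commonly left to a SAP. This stands in part: a reader might infer that the groups followed are certainly not the groups randomised, and the document does not support that. It depends on at least one club voting out and not being followed. What remains is a stated design feature. The vote concerns continuation in the study, it comes after allocation is known, and no published denominator rule keeps a departing club in.

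A reader might also infer that people are lost between the announcement in Jul/Aug 2017 and the start of data collection in Oct 2017. That rests on one loose timeline entry. The entry spans 24 months, whereas the data collection section says "Data will be collected for 27 months: 24 from the start of the study" plus three more, and it does not define the start. The gap is roughly one ordinary club visit interval and applies to both arms, and routine records could cover it. It is a reason to define time zero, not separate evidence of bias.

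A third tempting reading is that the bias favours the intervention. The most natural example points the other way: if clubs that hoped for fewer visits and drew SOC leave, and their retention would have been worse, SOC looks better and non-inferiority becomes harder to show. The direction is open.

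Finally, clubs have already passed one vote of more than 90%, so large exits cannot be presumed. That is fair, and it is why the working shows a range starting at 2%.

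**Conclusion.** The point holds as a conditional one. Whole randomised clubs can leave for reasons linked to their known arm, and nothing shown keeps them in the comparison. If any club does so, the arms compared are no longer those randomised. Bias is the main risk and its direction is unknown. It is about 0.1 to 2.3 points against a 10-point margin, on the assumption that 2-15% of one arm's clubs leave with retention 5-15 points lower. The loss of power is secondary. The number of clubs that left and their retention are not in the document, so no figure here estimates what happened.

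**What to change.** Keep the second vote, with its present meaning, as the safeguard against undue group influence. Add the following to the analysis plan:

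1. An all-randomised analysis that includes every consented member of every randomised club, in the allocated arm, with time zero at the date allocation was announced.
2. Passive follow-up of clubs that vote out, through the routine and provincial records already used for the primary outcomes. This applies where the signed consent or an ethics amendment permits it and the individual has not withdrawn permission for data use.
3. A per-protocol analysis beside it, with non-inferiority claimed only if both support it. Clubs that did not receive their allocated model pull the arms together in the all-randomised analysis, which favours a finding of non-inferiority.
4. A report, by arm, of club and member exits after allocation.

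The article says the final analysis had not yet begun, so this can still be written. The cost is wording, a check of the consent forms (possibly an ethics amendment), and some dilution in the all-randomised result.
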